**Research Plan:**

**Experimental Design:** Up to 40 (20 in gardening group and 20 in art group) participants will be recruited to take part in a series of GAs or AAs in experimental treatment sessions to take place over a four to five week period when greenhouse conditions are environmentally favorable. The experiment is designed to test for effects of engaging in group-based gardening or art on blood pressure and heart rate; satisfaction with leisure interests and relationships with friends; mental health which includes dimensions of depression symptomatology, anxiety, stress and mood disorder status; and overall quality of life of the participants. The purpose of this follow-up study is to determine whether there is a difference in treatment response by comparing assessments between the art and gardening groups using both physiological metrics and psychosocial measurements from both groups.

**Participant Eligibility Criteria:** We will select participants from a pool of potential volunteers assembled from respondents to a variety of print and broadcast advertisements, and those expressing interest resulting from word-of-mouth awareness of the recruitment efforts for the study. The study will focus on a wellness population, with similar eligibility criteria as the gardening study conducted in 2015. Participants must be 26-49 years of age, premenopausal women, preferably not pregnant at the time of enrollment in the study, be a non-gardener and non-artist, nonsmoker, in good health and have the ability to participate in all aspects of the study including working with plants in the greenhouse and working with art media in a conference room. Additional eligibility criteria include not having allergies to plants, plant parts like pollen, or plant-based foods, not having an addiction to alcohol or to recreational drugs or prescription medications, not suffering from recurring pain, exhibiting an average BMI less than 32 (a BMI chart will be provided for reference), and not having been diagnosed with any diseases, disorders or disabilities that presently negatively affect daily life. A screening questionnaire has been developed to reveal these health-related criteria (see In-Person Eligibility Screening Questionnaire Gardening and Art Study).

**Study Sample Size:** Based on a set of power calculations from the previous gardening pilot study (IRB201400425), we estimate needing up to 20 individuals in each of the experimental conditions, i.e. gardening program and art program. We will consider the study fully enrolled when 40 study participants are deemed eligible and ready to participate in the experimental intervention. Based on power calculations of psychometric data from the previous gardening study, minimum estimated sample sizes range from 12 to 17 participants required for the gardening experimental condition to achieve sufficient power. However, it is anticipated that perhaps as many as 50% of consented volunteers may fail one or more eligibility requirements, or elect not to continue in the experimental stage of the study.

We anticipate over the experimental treatment duration, that some participants might experience a life event (illness, loss of a loved one, serious accident or similar occurrences) that makes it necessary for them to withdraw from the study prior to study completion. Others may simply decide to cease participating. Some participants may miss some of the sessions. We believe the study, if fully populated, can sustain a 20% attrition rate in either of the two treatment groups and still provide valuable scientific information. Study staff will keep records of participant attendance. We have arbitrarily set an attendance minimum of 6/8 GA or AA sessions for the inclusion of data from a subject. Participants that have a major life event or miss more than two sessions will be allowed to attend all remaining gardening or art sessions. However, no further data from a subject will be collected following the third missed gardening or art session. Any collected data from such participants will be flagged and excluded from data analyses as determined to be scientifically appropriate.

**Staging of Experimental Gardening and Art Programs:** The experimental design for the GA and AA programs will consist of twice weekly group sessions of up to a maximum of 10 participants in an individual session and totaling up to 20 participants overall in each of the treatment group cohorts. Both GA and AA sessions will be approximately 60 minutes in duration and will take place in the Therapeutic Horticulture Greenhouse at Wilmot Gardens or a multi-purpose room in the Conference Center at Wilmot Gardens. Gardening and art sessions will take place on the same day(s) and at the same time. A total of eight individual gardening activity sessions and eight individual art activity sessions will be conducted over a period of four weeks. There will be two GA treatment sessions per week, and two AA sessions per week. Participants will be assigned to attend sessions occurring on Monday and Wednesday or Tuesday and Thursday. If participants are absent from a session, there will be no opportunity to make-up the session. If a study subject misses more than 2 sessions, any further data collected will be excluded from the data set, and the participant will be dropped from the study. An AHTA-registered, master-level horticultural therapist (Co-Principal Investigator) will review each GA experimental treatment planned. A Master’s student and Study Coordinator ([name]) and/or the Principal Investigator ([name]) or other study staff member will lead each individual gardening activity session. [name] will monitor the gardening and art sessions as necessary to confirm experimental comparability. Each art activity will be reviewed and administered by a professional artist(s) and/or experienced personnel in the UF Arts in Medicine program. Each individual gardening and art activity session will tightly follow the same sequence (Table 1).

The experimental design of the study is upgraded from the previous gardening study protocol executed in spring 2015. Previously, the design implemented a protocol in which women self-selected to be in a treatment group or non-active control group. The current design includes the alternate, comparable group of art activity. Eligible volunteers will be screened, consented, selected and enrolled in the study. Participants will then be randomly assigned to receive either the gardening treatment intervention or art intervention. Further participant assignment into two subgroups of gardening and art will be random, but it may be necessary to adjust some assignments to accommodate participant schedules. Both treatment groups will undergo the same self-report psychological and social assessments and physiological measures along the same timeline with congruent intervals of administration.

If study volunteers are eligible, they will be enrolled in the study and invited to attend an orientation session for either the art or gardening groups that includes a tour of the facilities, parking instruction, rules of the experiment, introductions of the group members to study staff and other members of the groups. This is when baseline psychometric assessments will be given.

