This proposed study is a follow-on study to a gardening study conducted at Wilmot Gardens in 2015 (IRB 201400425). The previous study revealed therapeutic benefits for study participants in a gardening treatment group compared to a no treatment concurrent control group (unpublished data). In part, this proposed study is designed to follow the earlier gardening study, while improving and reducing potential for bias in the experimental design with the addition of an active concurrent control group, in the form of an arts program. This design model allows for statistical analyses of relative-effect estimates as compared to absolute-effect estimates.

The reasons for selecting an all women, wellness study population are several-fold. There are known cultural, societal and sex differences in the way males and females respond to interactions with plants, and these factors are reflected in part by known consumer patterns. For example, Japanese men were less favorable towards the presence of street-side flowers compared to trees than women (Todorova et al 2004). More women than men agreed with statements that gardening satisfaction is peace/tranquility and plants make me feel calmer/more relaxed in a study of attitudes towards plants and gardening (Relf et al 1992). Women exhibited a stronger flower color preference than men when purchasing geraniums (Behe et al 1999). In a study of images of natural environments versus urban settings, Ulrich and colleagues (1981) found significant sex differences in the responses of women and men with respect to positive affect and attentiveness. Both aspects of psychological status declined more when women viewed urban scenes than they did for men. In a study of garden centers and mass merchandisers, it was found that 85% of shoppers were female and 58% were between the ages of 25 and 55 (Yue and Behe 2009). According to the Society of American Florists, men spend more on floral gifts, and more men than women buy roses and floral arrangements valued above $30. In contrast, women buy a wider range of floral gifts at a lower cost, and more women than men buy less expensive loose or bunched flowers, floral arrangements, flowering plants and dish gardens (<http://www.safnow.org/>).

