Additionally, there appears to be evidence for sex differences in stimulus processing in the brain, particularly with respect to responses to various stimuli including visual stimuli (Klein et al 2003; Wrase et al 2003; Smeets et al 2006; Garn et al 2009; Frank et al 2010) in a number of fMRI studies. We believe a study population of a single sex, in this case only women, will reduce experimental variability and increase the probability of detecting a biological effect of the experimental treatment (McCarthy et al 2012). Moreover, it may be that some of the best-documented benefits of working and interacting with plants align well with disorders known to be more prevalent in women such as depression, Multiple Sclerosis, Chronic Fatigue Syndrome and Celiac Disease. We do understand over the time course of the proposed experimental treatment, participants’ menstrual cycle may contribute to variability in the experimental results.

The objectives of this research are three-fold:

1. Ascertain if engaging in a group-based gardening program will differentially alter the mental health status and/or quality of life of healthy women compared to engaging in a group-based art program.
2. Determine if engaging in a group-based gardening program will differentially alter satisfaction with participation in discretionary social activities compared to engaging in a group-based art program.
3. Establish whether blood pressure and/or heart rate will change relative to involvement in a group-based gardening program compared to a group-based art program.

The hypotheses, listed below, will be tested with a well-defined wellness population of women as detailed in a later section of this protocol (see Participant Eligibility Criteria section below). Assessment of the effects of the group-based gardening activity (GA) or art activity (AA) on the experimental populations will take two approaches, the first being the use of wrist cuff blood pressure monitors on the participants to assess systolic and diastolic blood pressure and heart rate that may be improved as a consequence of experiencing the cumulative gardening or art programs and associated stimuli. The second approach will employ widely used and well-established self-reported psychometric assessment instruments that will capture information about the health and well-being of participants.

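### The pilot-based sample size statement (12 to 17, planned 20 per arm) does not support the power of the randomised gardening-versus-art comparison

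*Protocol*

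**What the plan says.** The sample size rests on one source. The Study Sample Size paragraph of the Protocol opens "Based on a set of power calculations from the previous gardening pilot study" and continues "we estimate needing up to 20 individuals in each of the experimental conditions, i.e. gardening program and art program". It then adds, from the psychometric data of that same study, that "minimum estimated sample sizes range from 12 to 17 participants required for the gardening experimental condition to achieve sufficient power". It also says that the study can tolerate 20% attrition in either arm.

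Two other places describe the earlier study. The Background reports "therapeutic benefits for study participants in a gardening treatment group compared to a no treatment concurrent control group (unpublished data". The Staging of Experimental Gardening and Art Programs section says that in it "women self-selected to be in a treatment group or non-active control group".

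The present trial differs on both counts. The same Staging section says "Participants will then be randomly assigned to receive either the gardening treatment intervention or art intervention", and the first objective in the Background is to "Ascertain if engaging in a group-based gardening program will differentially alter the mental health status and/or quality of life of healthy women", with the art programme as comparator. The Experimental Design paragraph gives the between-group comparison as the purpose of the study, and hypothesis 1 under Specific Aims is a between-group difference.

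**The concern.** A sample size carries over from one study to another only if the effect it was sized on is the effect now being tested. The pilot contrast was gardening against nothing among women who had picked their group. It therefore mixes the effect of gardening with the effects of attention, group contact, expectation and self-selection. The new contrast is gardening against another structured, staff-led group activity, under randomisation.

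The protocol itself expects the new comparator to be active. Specific Aims predicts parallel gains in social satisfaction, and lower blood pressure and heart rate in both groups. The Health and QOL Evaluations section links art programmes to better anxiety, depression and quality of life. The Art Activities section says the art sessions were designed to match gardening in physical, cognitive and social engagement. On that reasoning the gardening–art difference is plausibly smaller than the pilot difference. The Background even notes that the new design moves from absolute to relative effects, yet the sizing paragraph describes no adjustment.

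What is at stake is how the result is read. Hypothesis 2 predicts that the two groups will improve in parallel. If readers accept that power was sufficient, a non-significant difference could be taken to show that art works as well as gardening, when the data may be compatible with a sizeable difference either way.

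**Working it through.** **Inputs from the Protocol.** Minimum 12 to 17 for the gardening condition; up to 20 per arm planned; 20% attrition tolerated (all Study Sample Size).

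**Assumptions.** The protocol gives no significance level, power, effect size, SD, instrument or test behind these figures. I assume a two-sided 5% level, 80% power and an unadjusted two-sample t-test at one time point.

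**Step 1: reproduce the plan's figure.** This is not possible without the pilot effect and SD. What can be done is to solve for the standardised effect d that would give 12 or 17 per group.

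Normal approximation: d = (1.960 + 0.842) × √(2/n).
- n = 12: 2.802 × 0.408 = 1.14
- n = 17: 2.802 × 0.343 = 0.96

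The exact noncentral-t solution is d = 1.20 at n = 12 and 0.99 at n = 17. Other conventions move this range: one-sided 5% at 80% power gives 1.05 to 0.87, and two-sided 5% at 90% power gives 1.39 to 1.15. If the calculation was instead a before–after test within the gardening group, n = 12 to 17 implies a standardised change of 0.89 to 0.72.

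**Step 2: carry the implied effect to gardening versus art.** The documents do not say what share of the pilot effect would remain against art, so a range is shown. In each cell the first figure starts from n = 12 and the second from n = 17 (noncentral t).

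| Share kept | d | Power, 20 per arm | Power, 16 per arm | n per arm for 80% |
| --- | --- | --- | --- | --- |
| 100% | 1.20, 0.99 | 96%, 86% | 91%, 77% | 12, 17 |
| 75% | 0.90, 0.74 | 79%, 63% | 69%, 53% | 21, 30 |
| 50% | 0.60, 0.50 | 45%, 33% | 37%, 27% | 45, 65 |
| 25% | 0.30, 0.25 | 15%, 12% | 13%, 10% | 177, 257 |

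Under the within-group reading, even a gardening–art difference in change as large as the whole gardening change (0.89 to 0.72 SD of change) needs 21 to 31 per arm.

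**Step 3: what the planned size can detect.** With 80% power under the same assumptions, the detectable difference is 0.91 SD at 20 per arm and 1.02 SD at 16 per arm. At 20 per arm, the 95% confidence interval for the difference has a half-width of about 2.02 × √(2/20) = 0.64 SD.

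**Step 4: attrition.** 20 × 0.80 = 16 per arm, which is below the protocol's own upper minimum of 17. Keeping 17 after 20% loss takes 17/0.80 = 21.25, that is 22 per arm.

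**The case against.** Several points on the other side are fair.

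- **The numbers may still be adequate.** With no pilot effect stated, nothing shows that 20 per arm is wrong. The inputs may stand in a statistical analysis plan that is not at hand, so their absence is not the point here. This stands, and it limits the conclusion to lack of support.
- **The effect need not be smaller.** A reader might infer that the gardening–art difference has to be below the pilot difference. The documents do not go that far. The Background's review of art therapy is mixed: one review found inconclusive support, one meta-analysis found no significant effect on depression or quality of life, and another review found improvement in both. Self-selection could also have biased the pilot in either direction. Plausibly smaller is as far as the text allows.
- **The 12–17 figure is a minimum for one condition, and 20 are planned.** A single-group figure has some use, since hypothesis 3 concerns change in both groups. But 12–17 comes from psychometric data while hypothesis 3 concerns blood pressure and heart rate, and the 20 is drawn from the same pilot. The larger number does not cure the mismatch.
- **The detectable difference depends on the analysis.** Baseline scores are collected. Adjusting for them would give roughly 0.91 × √(1 − r²), which is 0.79 SD at an assumed correlation of 0.5 and 0.65 SD at 0.7. Delivery in groups of up to 10 works the other way: an assumed intraclass correlation of 0.05 gives a design effect of 1 + 9 × 0.05 = 1.45 and a detectable difference of 0.91 × √1.45, about 1.09 SD. This stands, so any stated figure should carry its assumptions.

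**Conclusion.** The concern holds in a limited form. The protocol presents a power basis from self-selected gardening versus no treatment, and it does not support the power of a randomised gardening-versus-art comparison. The 12–17 figure would carry over only if gardening beat art by as much as it beat no treatment in the pilot, and nothing in the protocol argues for that.

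The size of the shortfall cannot be fixed. Under the stated assumptions, power at 20 per arm runs from 79–63% down to 15–12% as the share of the implied pilot effect that remains falls from 75% to 25%. It would be a mistake to quote any one row, such as 45–33% at half the effect, as the power of this trial, because the documents support no particular share. Nor do they show that the trial is too small. Separately from these assumptions, the attrition that the protocol accepts takes an arm below its own upper minimum, 16 against 17.

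**What to change.** Change the Study Sample Size paragraph; no participants are added.

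1. Remove the 12–17 range as evidence of sufficient power for the gardening–art comparison, or state that it refers only to the earlier gardening study.
2. State that the earlier study had a no-treatment comparator and self-selected groups, so its sizing is not specific to gardening versus art.
3. Give the detectable difference with its assumptions: about 0.91 SD at 20 per arm and 1.02 SD at 16 per arm, for an unadjusted two-sample t-test at a two-sided 5% level and 80% power. Add that it becomes smaller with baseline adjustment and larger with clustering by session group.
4. Say that between-arm results will be reported as estimates with confidence intervals, and that a non-significant difference will not be read as equivalence of the two programmes.

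The cost is a less favourable power statement. The change does not raise the power; it makes the protocol say accurately what the planned size can show.

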**Reimbursement of Participation Costs:** To defray the costs associated with transportation and parking, the study will offer compensation up to the amount of $60 in gift cards for each participant who attends at least six of the gardening sessions, with payments of $20 at visits 2, 6 and 10. Participants in the gardening program will also receive a plant guidebook (“Florida Gardener’s Handbook” by MacCubbin, Tasker, Bowden and Lamp’l, 2012; valued at $24.00 containing information about most of the plants used in the GA. Participants in the gardening program will also be able take home the containerized plantings and individual plants generated from the activities. Total value for take home items from the GAs is estimated at $100 per participant. The participants in the art program will also receive up to $60 compensation, with payments of $20 at visits 2, 6 and 10. Participants in the art program will also be able to take home any art projects they have worked on during the program and an art guidebook (“The Artist’s Handbook” by Ray Smith, 2009) valued at $16.00 containing information about art techniques similar to those learned in the AAs. The value for the take home items for the AAs is estimated at $100. All participants will be asked to a sign a receipt, and study staff will track monetary compensation during the course of the experiments.

Conflict of Interest:

The study team does not have any conflict of interests to disclose.

References:

Andrews, L.W. (2013). Minding the Body: Nine ways to relieve stress by gardening. Psychology Today. April 1, 2013. <http://www.psychologytoday.com/blog/minding-the-body/201304/nine-ways-relieve-stress-gardening> Accessed June 2, 2014.

ATUS 2003-2015. US Department of Labor, Bureau of Labor Statistics and US Department of Commerce, US Census Bureau. American Time Use Survey. <https://www.bls.gov/tus/datafiles_0315.htm>. Accessed June 27, 2017.

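### Data collection stops at the third missed session and inclusion depends on attending 6 of 8 sessions, so the gardening–art comparison is no longer between the groups as randomised

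*Protocol*

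**What the plan says.** Under Staging of Experimental Gardening and Art Programs, the protocol sets out a randomised design: "Participants will then be randomly assigned to receive either the gardening treatment intervention or art intervention". Under Experimental Design, the purpose is to "determine whether there is a difference in treatment response by comparing assessments between the art and gardening groups".

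Study Sample Size then sets three rules on attendance:

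- A threshold: "We have arbitrarily set an attendance minimum of 6/8 GA or AA sessions for the inclusion of data from a subject".
- A stop: "However, no further data from a subject will be collected following the third missed gardening or art session". The sentence before it lets women who pass two absences, or who have a major life event, attend the remaining sessions.
- A rule for data already in hand: "Any collected data from such participants will be flagged and excluded from data analyses as determined to be scientifically appropriate".

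The Staging section states the rule again. Missed sessions cannot be made up, and after more than two absences "any further data collected will be excluded from the data set, and the participant will be dropped from the study".

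The Health and QOL Evaluations section gives SF-36, STAI and SPDSA at visits 2 and 11 only. POMS and PSS are also given at visits 4, 6, 8 and 10, and BDI-II at visits 6 and 10. Data Collection places visit 11 after the eighth session.

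**The concern.** Attendance happens after randomisation. It can depend on the activity a woman was assigned and on how she feels, and mood, stress and depression are among the outcomes. Study Sample Size itself expects some women to leave after illness or bereavement and others by choice. If the two programmes lose different women, a difference between the remaining groups can reflect who remained and not what the programmes did.

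An analysis plan usually chooses the analysis set, and a poor choice there can be corrected later. This one cannot, because the protocol tells staff not to collect the outcome. The final battery would not exist for these women, even for those still coming to sessions. The sponsor could then neither run a complete as-randomised analysis nor show that the exclusions did no harm.

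**Working it through.** **1. Which data are lost.** Visit 2 is the orientation, visits 3 to 10 are sessions 1 to 8, and visit 11 is the wrap-up. A third absence can occur at session 8 (visit 10) at the latest, so visit 11 always falls after it. Every woman with three absences therefore loses the visit-11 battery. For SF-36, STAI and SPDSA that leaves no post-baseline value. For POMS, PSS and BDI-II some mid-course values may exist, but not the final one. The first two hypotheses under Specific Aims (mental health and quality of life; social satisfaction) rest on these instruments.

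**2. The statements side by side, for a woman with three absences.**

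| Statement | Data before the third absence | Data after it | May she attend? |
|---|---|---|---|
| Study Sample Size, 6-of-8 threshold | Not included | Not included | – |
| Study Sample Size, stop and exclusion sentences | Excluded if judged appropriate; no criterion or decision-maker | Not collected | Yes |
| Staging section | Not mentioned; only later data are excluded | Excluded | Dropped from the study |

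The statements lead to different analysis sets: none of her data, an undetermined part, or everything up to the third absence. The exclusion sentence can also be read to cover a woman with a life event who met the 6-of-8 minimum.

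**3. How large the bias could be.** The protocol gives no figure for this. Its sample-size range (12 to 17) cannot be reproduced, because no significance level, power, effect size or SD is stated; the point does not depend on it. The following is an illustration.

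Inputs:
- 20 women per arm (Study Sample Size).
- Share excluded, q: 20%, borrowed from the attrition rate the protocol says it can sustain, and 10% as a milder value (assumption).
- Correlation r between attendance propensity and outcome: 0.3 to 0.7 (assumption; nothing in the protocol fixes it).
- No true difference between arms.

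Formula: excluding the lowest fraction q on attendance propensity shifts that arm's mean by r × φ(z_q)/(1 − q), in SD units.

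- q = 20%: φ(z) = 0.280, and 0.280/0.80 = 0.350.
- q = 10%: φ(z) = 0.1755, and 0.1755/0.90 = 0.195.

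The between-arm bias is r times the difference of these factors. The type I error of a nominal two-sided 5% test (normal approximation) uses SE = √(1/n₁ + 1/n₂).

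| Excluded, arm A vs arm B | Factor | Bias at r = 0.3 / 0.5 / 0.7 (SD) | SE | Type I error |
|---|---|---|---|---|
| 20% vs 0% (16 vs 20 women) | 0.350 | 0.105 / 0.175 / 0.245 | 0.335 | 6% / 8% / 11% |
| 20% vs 10% (16 vs 18 women) | 0.350 − 0.195 = 0.155 | 0.05 / 0.08 / 0.11 | 0.344 | 5% / 6% / 6% |
| Equal shares, same mechanism | 0 | 0 | – | 5% |

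**The case against.** The strongest reply is that the rule is fixed in advance and identical in both arms, and that the programmes are built to be alike. Sessions run on the same days and at the same time, physical, cognitive and social demands are matched, the greenhouse is cooled and shaded, participants are neither gardeners nor artists, and take-home items are valued at about $100 in each arm. Since the aims concern engaging in a programme, an attender set has some rationale. The choice of main analysis set is also often left to an analysis plan.

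Much of this stands. It makes a large difference in attendance between arms less likely, and it justifies keeping the 6-of-8 set as a secondary look. It does not answer the stop in data collection: a matched design reduces the chance of differential loss but does not exclude it, and no analysis plan can use measurements that were never taken.

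A reader might infer several stronger points that the protocol does not support:

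- **Unblinded staff remove data at their discretion.** No decision-maker is named and blinding is not described. What can be criticised is the missing criterion.
- **The analysed groups are purely self-selected.** Some absences are involuntary, such as illness, accident or bereavement. Selection on attendance occurs either way, but not always by choice.
- **All of the tolerated 20% loss, and the power that goes with it, is due to this rule.** That figure is general attrition, and some of those women would be missing under any rule.
- **The payment schedule drives the loss.** The six-session wording under Reimbursement of Participation Costs appears for gardening only ("for each participant who attends at least six of the gardening sessions, with payments of $20 at visits 2, 6 and 10"), but nothing links payment to missing visit-11 data. Moving a payment to visit 11 would cost $20 to a woman who attends visit 10 and misses visit 11.

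**Conclusion.** The point holds. Conditioning inclusion on a post-randomisation attendance cut-off, and ceasing to measure women who fall below it, means the planned comparison is not between the groups as randomised. The loss of the visit-11 SF-36, STAI and SPDSA cannot be reversed. The exclusion of earlier data has no stated criterion, and the two sections define the affected data differently.

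The size of the bias is unknown. Under assumed correlations of 0.3 to 0.7 it is about 0.10 to 0.25 SD when one arm excludes 20% and the other nobody, which is an extreme case. It is about 0.05 to 0.11 SD at 20% versus 10%, and zero if exclusion rates and mechanism are equal. The upper figure should not be read as the expected bias: the protocol gives no evidence that attendance will differ by arm. The case for change is that the comparison is exposed without need and the damage could not be assessed afterwards.

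**What to change.** Amend the protocol as follows:

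1. Seek the visit-11 battery from every randomised participant who has not withdrawn consent, whatever her attendance.
2. Make the main analysis all randomised participants, each in her assigned arm.
3. Use the at-least-6-of-8 set as a sensitivity analysis only. Attendance flags can stay, to define that set.
4. Delete the discretionary exclusion clause in Study Sample Size.
5. Reconcile Study Sample Size with the Staging section, so that one rule states what happens to data collected before and after the third absence, and whether the woman remains in the study.

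The cost is a short amendment and a few extra visit-11 questionnaires. The estimated effect may be slightly diluted compared with an analysis of attenders only, and the sensitivity analysis would show by how much the two differ.
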